## Abstract

**Background:**

Most people prefer home palliation but die in an institution. Some experience decisional conflict when weighing options regarding place of care. Clinicians can identify patients' decisional needs and provide decision support, yet generally lack skills and confidence in doing so. This study aims to determine whether the quality of clinicians' decision support can be improved with a brief, theory-based, skills-building intervention.

**Theory:**

The Ottawa Decision Support Framework (ODSF) guides an evidence based, practical approach to assist clinicians in providing high-quality decision support. The ODSF proposes that decisional needs [personal uncertainty, knowledge, values clarity, support, personal characteristics] strongly influence the quality of decisions patients make. Clinicians can improve decision quality by providing decision support to address decisional needs [clarify decisional needs, provide facts and probabilities, clarify values, support/guide deliberation, monitor/facilitate progress].

**Methods/Design:**

The efficacy of a brief education intervention will be assessed in a two-phase study. In phase one a focused needs assessment will be conducted with key informants. Phase two is a randomized control trial where clinicians will be randomly allocated to an intervention or control group. The intervention, informed by the needs assessment, knowledge transfer best practices and the ODSF, comprises an online tutorial; an interactive skills building workshop; a decision support protocol; performance feedback, and educational outreach. Participants will be assessed: a) at baseline (quality of decision support); b) after the tutorial (knowledge); and c) four weeks after the other interventions (quality of decision support, intention to incorporate decision support into practice and perceived usefulness of intervention components). Between group differences in the primary outcome (quality of decision support scores) will be analyzed using ANOVA.

**Discussion:**

Few studies have investigated the efficacy of an evidence-based, theory guided intervention aimed at assisting clinicians to strengthen their patient decision support skills. Expanding our understanding of how clinicians can best support palliative patients' decision-making will help to inform best practices in patient-centered palliative care. There is potential transferability of lessons learned to other care situations such as chronic condition management, advance directives and anticipatory care planning. Should the efficacy evaluation reveal clear improvements in the quality of decision support provided by clinicians who received the intervention, a larger scale implementation and effectiveness trial will be considered.

**Trial registration:**

This study is registered as NCT00614003

## Background

There are more choices for place of end-of-life cancer care due to shifts in care to the community, better understanding of the clinical course of cancers, equipment portability, pharmacology advances, and consumer expectations. Place of care has various meanings to patients and families and represents more than a particular geographic location [1]. Options can include hospice, private residence, nursing home, continuing complex care facility, homeless shelter, and/or hospital. For patients with good symptom control, instrumental support, and a predictable course of illness, decisions regarding place of care are often based on values and expectations [2-5].

Patients frequently experience decisional conflict (personal uncertainty about the best course of action) when considering place for end-of-life care. Personal preferences are weighed against practical considerations and concern for others [2,3,5,6], thus contributing to decisional conflict. Other modifiable factors such as knowledge gaps, unrealistic expectations about outcomes, lack of clarity about what matters most, and feeling pressured to choose a particular option exacerbates the decisional conflict [7]. Unresolved decisional conflict can lead to decisional delay or reversal, dissatisfaction, regret, and blaming the provider [8,9]. Failure to elicit the valued priorities of terminally ill patients and their families can result in missed opportunities, decreased quality of life, unwelcome interventions, and increased risk for complicated bereavement for survivors [3,10-12].

It is generally known that decisional conflict can be reduced with decision support interventions such as decision aids and nurse coaching [7,13]. However, there have been few studies evaluating either of these interventions for decisions at the end-of-life. Although patient decision aids may be useful for some common discrete crossroads decisions with standardized options and outcomes, there may be more payoffs in focusing on coaching interventions that can be applied broadly to care management at the end-of-life. While end-of-life decisions are highly values-sensitive, they also bear a strong resemblance to chronic condition management decisions, which focus on situation monitoring, priority setting, and implementation [14-16].

There is evidence that influencing practitioners' knowledge and attitudes about communication and decision support can strengthen subsequent decision support practices, thus matching care planning to patient preferences and avoiding the use of non-valued interventions [17-20]. Nevertheless few studies have empirically examined the impact of a theoretically informed, decision support training intervention on the quality of decision support knowledge and practices provided by practitioners [21] and none have been undertaken within the context of palliative care practice.

Patients and families want clinicians to listen to their views and preferences [18] and standard palliative practice calls for patient inclusion in care planning [22,23]. Most patients with advanced cancer want full information and the majority wish to participate actively in decision making [24]. Although seriously ill hospital patients want to discuss end-of-life issues, their preferred decision making role varies and is difficult to predict [25], highlighting the need for active and regular assessment of patients' decision making needs. However, clinicians may avoid raising uncomfortable topics [26-28] and often lack skills and confidence in helping patients in non-directive ways [29].

Systematic review findings confirm that training clinicians in patient centered approaches is an effective strategy for increasing patients understanding of the evidence and implications [30]. For instance, decision coaching by nurses has helped to foster an informed use of resources and avoid the over-use of interventions that patients don't value in urology care [17] and in gynecological care [31]. Practitioners, such as nurses and other professional care coordinators, through their trusted and frequent interactions with patients are well positioned to elicit and explore decisional needs such as decisional conflict and related factors (e.g.: knowledge, values clarity, and support) [32]. Practitioners can then coach patients with information, values clarification, support and links to resources. While a key challenge is the need to strengthen practitioners' decision support skills [29] training interventions have been shown to markedly improve the quality of practitioners' decision support skills for other clinical problems [33].

Accountability to quality patient outcomes and fiscal responsibility confirms the need to practically and pragmatically address patients' end-of-life decision making needs. Systematic and rigorous evaluation of an evidence-based intervention designed to improve the quality of practitioners' decision support could illuminate best practices for decision support and advance the fields of shared decision making, patient-practitioner communication, palliative care, and ultimately improve the lives of those who are living with a terminal illness and their families.

Multifaceted interventions show promise in influencing professional behavior change [34-37]. An exploratory study to identify target variables, choose and refine interventions, and establish their theoretical basis prior to large scale effectiveness trials is a sound research approach [38-40]. The paucity of empirical inquiry, in this area to date, warrants an exploratory study to describe the constant and variable components of a potential intervention and a feasible protocol for intervention delivery.

### Guiding Theoretical Models

As the study aims to influence decision support behavior an understanding of factors that can be partially modified, such as attitudes and perceptions of norms that drive actions, is required to inform intervention messages and enhance the potential for behavior change. The pragmatic and conceptual focus of the study also requires an empirically proven, clinically relevant decision support framework to guide intervention content. The Theory of Planned Behavior (TPB) [41,42] and the Ottawa Decision Support Framework (ODSF) [43] fit these criteria. The former predicts the likelihood of behavior change while the latter provides a three step path to optimize quality decision support. The TBP [40,44-46] and the ODSF [3,47,48] are relevant to nursing and have performed well in numerous health-related studies.

Briefly, the TPB proposes that the strength of the intention to change is the primary determinant of actual behavior change. This intention is determined by: (1) a person's attitude to the new behavior (strength of perceived advantages and disadvantages); (2) the extent of self-perceived social pressure to perform or not to perform the new behavior, and (3) degree of perceived control over being able to perform the behavior [49].

According to the ODSF, decision support interventions can be tailored to address modifiable determinants of decisional conflict (knowledge; outcome expectations; values clarity ; support factors) resulting in better quality decisions that are informed and consistent with patients' values [50]. In this study, the ODSF will guide decision support skill acquisition interventions and measures of change.

Clinician-identified factors associated with practice change: utility, strong evidence basis, and flexibility to acknowledge the individuality of patients [51] fit well with the ODSF. Historically, the ODSF has been well received by clinicians [3,33,48], has shown robustness in randomized control studies [7,33] and is predicated on a patient-centered approach which recognizes the unique context, circumstance and patient characteristics situated within the decision support encounter. The TPB and ODSF have guided the study design in the following ways:

1. The predictive potential of theory facilitates selection of training intervention components which offers the best probability of success [36,52].

2. The TPB offers a useful lens to examine attitudes, beliefs and perceived control for engaging in decision support practices and will inform the selection of key messages attached to intervention strategies.

3. Mapping the intervention components onto TPB variables provides a useful template to ensure multiple targets of behavior change are addressed and is consistent with knowledge dissemination best practices [35,53].

4. The ODSF describes a well defined approach to quality decision support provision and provides a practical vehicle to structure components of a knowledge and skill building intervention.

5. Availability of a broad inventory of theoretically grounded and empirically validated, reliable, time tested tools operationalizing ODSF constructs provides a rigorous platform to inform study interventions and will strengthen the trustworthiness of study findings.

## Methods/Design

### Aims of the study

The primary aim of this study is to evaluate the efficacy of a theory driven, framework-based training intervention, as compared with a control condition (usual care approach) in enhancing the quality of practitioners' patient decision support skills regarding place of care at end of life. In addition, we plan to assess participants' intention to engage in patient decision support in their practice and to determine the acceptability of the intervention components. Specific objectives include:

1. To identify factors affecting the likelihood of practitioners' integrating decision support principles into their practice

2. To determine the quality of decision support practitioners provide

3. To design and evaluate components of a decision support training intervention

We plan to test the following study hypothesis:

**H_1_**: A significantly greater proportion of practicioners, who are randomized to a multi-faceted, theory driven, training intervention, will obtain higher scores on quality of decision support following the intervention

**H_0_**: No change in group means in decision quality following the intervention

#### Study Design and Methods

A two phase, sequential, mixed method design is planned.

**Phase 1 **involves a focused needs assessment of key informants (clinicians, educators, administrators) who plan and provide palliative/oncology care. A purposive sample of about 12 key informants representing different levels of experience, responsibility, clinical focus and setting will be interviewed using a semi-structured interview based on the TBP [54].

**Phase 2 **is a randomized control trial of a brief educational intervention. Consenting/eligible participants will be randomly allocated to an intervention or control group. The intervention, informed by the needs assessment, comprises: an online tutorial; an interactive skills building workshop, a decision support protocol; performance feedback, and educational outreach.

Participants will be assessed: a) at baseline (quality of decision support); b) after the tutorial (knowledge); and 3–6 weeks after the other interventions (quality of decision support; intention to adopt decision support into clinical practice).

#### Sample Size

The estimated sample size for the Phase 2 study is based on a test for differences in mean scores of decision support quality and knowledge in the intervention versus the control group. An effect size of .70 requires n = 32/group, when alpha error = 0.05 and beta error = 0.20 [55]. This effect size is conservative in that a previous study (17) reported larger effect sizes which required only 18–20 per group.

#### Participants

Full or part time nurses and care coordinators (i.e.: social worker, case managers, pharmacists) from three Ontario regions (Ottawa, Toronto, Kingston), employed by one of the ten study partner organizations will be invited to participate. Study partners include hospital based institutions [Ottawa Hospital, Queensway-Carleton Hospital, SCO Health Services], community based organizations [Community Care Access Center Care (Toronto Central; Southeast Ontario); CareFor Nursing Agency; St. Elizabeth Health Care (Toronto, Kingston); Hospice at May Court; Bayshore Home Health Agency (Cornwall, Toronto, Ottawa)]. Information flyers and information sessions explaining the study will be held at study partner organizations. Interested potential participants will be asked to contact the study coordinator if they have further questions or would like to participate in the study. Participants are considered eligible for study inclusion when they meet the following criteria:

• are a member of a regulated health profession

• care for palliative cancer patients, and/or

• cancer patients with advanced disease, and

• work at least 4 shifts per month,

• in a clinical area where end of life care discussions are likely to be undertaken, and

• are proficient in written and spoken English.

#### Ethical considerations

The protocol has been approved by the Research Ethics Committees of the University of Ottawa, The Ottawa Hospital and SCO Health Services. Trial registration with the International Standard Randomized Controlled Registry has been obtained (Trial #NCT00614003).

#### Procedures

##### Phase 1: Needs Assessment

Semi-structured interviews with a purposive sample of key informants (n ≅ 12 engaged in direct care, education and/or administration roles) will be used to elicit TPB related factors affecting intentions to provide decision support (personal attitudes, norms, and perceived control). Questions about other barriers to providing decision support will be elicited. Results will inform intervention content and key messages.

##### Phase 2 Intervention

Consenting practitioners will be randomly allocated to one of two groups. A computer generated randomization list for concealed allocation will be used. To avoid disparate sample sizes permuted blocks will be used. Participants will be allocated by an external statistician, who has no connection to the study team, immediately after collection of baseline data.

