##### 2. Intervention (experimental) group

Participants assigned to the intervention group will:

a. Complete an on-line decision support tutorial which introduces the 'When you need extra care decision aid', case studies and quizzes related to place of care decision support.

b. Participate in a half day skills building workshop. The workshop contains aggregated feedback on baseline simulated calls; opportunities to observe, compare and contrast a traditional patient education approach to a patient decision support approach; role play using the 'When you need extra care decision aid' and peer scoring of the quality of their decision support provision using the DSAT. A determinants of place of care knowledge module will also be delivered. At the end of the workshop, participants will complete a questionnaire eliciting perceived utility/usability of the a) workshop content, and b) decision support protocol.

c. Participate via telephone in an education outreach session to identify areas needing clarification, share problem solving in using the decision support protocol, and to obtain further feedback.

d. Complete a questionnaire eliciting satisfaction with content and process of education program.

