### Analysis Plan

#### Primary Outcome Phase 2: Quality of nurses' decision support skills

1. Inter-rater reliability of DSAT scores; two raters, who are blind to group allocation, will independently score pre and post intervention simulated call audio tapes.

2. Primary analysis will be undertaken using a repeated measures ANOVA (baseline; post measures). For missing cases an 'intention to treat', approach will be used under the conservative assumption that no change would occur between pre and post testing. Additionally, the impact of missing cases on findings will be explored between groups to provide further direction for the analysis.

#### Secondary outcomes Phase 2

1. Descriptive measures (frequency; means; range) will describe participant characteristics and acceptability and utility of training intervention components.

2. Descriptive measures (frequency; means; range) of the TPB based survey eliciting behavioral intention to integrate decision support in practice and related attitudes, norms, and perceived control will be undertaken. Between group differences in intention to integrate decision support practices will be analyzed using a t test.

3. Data from qualitative open-ended questions using traditional content analysis techniques [69,70] with the TPB as an organizing framework will be undertaken. Thematic coding, followed by member checking to ensure trustworthiness of final themes, will be undertaken.

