## Discussion

This will be the first study to evaluate the impact of an educational intervention to improve the quality of decision support that practitioners provide to dying patients around place of care. This reproducible, portable intervention addresses a key policy mandate regarding choice for end of life care set out by health providers such as the Ontario Ministry of Health in Canada. This is a pragmatic trial with relatively inclusive entry criteria and we anticipate recruiting participants from across a spectrum of care sectors. As well, because we are bringing the intervention to participants in their home regions we are able to include participants who may be unable to access centrally held education due to time and distance pressures in their clinical setting. These features will improve the generalizability of the findings.

Expanding our understanding of how practitioners can best support palliative patients' decision making will help to improve the quality of end-of-life and care for patients and those who share their lives. If findings from this study show promise, a larger effectiveness trial assessing factors such as cost effectiveness, sustainability, and patient and system outcomes will be undertaken

Results will be disseminated via a brief summary prepared for policy makers, a communication flyer for participants, a technical report for the participating organizations, publication in refereed scientific journals, newsletters of palliative care and relevant clinician associations, presentations at scientific and clinical meetings, and clinical rounds. Findings will be available online through the websites of the Canadian Virtual Hospice, Canadian Institutes of Health Research (CIHR) Family Caregiving New Emerging Team, CIHR End-of-Life Care for Seniors New Emerging Team, and the CIHR/NCIC Strategic Training Program in Palliative Care Research.

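### Only the intervention arm is trained in shared regional workshops, but the sample size and the primary ANOVA make no allowance for it, so the interval is somewhat too narrow if scores correlate within a workshop

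*Protocol article*

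**What the plan says.** **Allocation.** The Phase 2 Intervention section of the protocol article randomises individuals: "Consenting practitioners will be randomly allocated to one of two groups". The one restriction is "To avoid disparate sample sizes permuted blocks will be used". No stratum is named. The Participants section draws staff from three regions (Ottawa, Toronto, Kingston) and ten partner organisations.

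**Delivery.** Under the intervention group's procedures, participants will "Participate in a half day skills building workshop". The sections on the workshop and on performance feedback describe role play, group discussion, and peers rating one another with tools based on the DSAT, which is also the primary outcome instrument. The control arm has no counterpart. The Discussion says the trial can reach more staff "because we are bringing the intervention to participants in their home regions".

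**Sample size.** The calculation is "based on a test for differences in mean scores of decision support quality and knowledge in the intervention versus the control group", and it states: "An effect size of .70 requires n = 32/group, when alpha error = 0.05 and beta error = 0.20".

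**Primary analysis.** "Primary analysis will be undertaken using a repeated measures ANOVA (baseline; post measures" is the stated method. No term for workshop, region or organisation is mentioned.

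**The concern.** People trained together share a facilitator, a discussion and a set of role-play partners. If that makes their later DSAT scores more alike, the intervention arm carries less independent information than its headcount suggests, while the control arm does not. An ANOVA that counts every participant as independent then reports too small a standard error and too narrow an interval for the group difference.

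The article says that promising findings will lead to a larger effectiveness trial. The precision claimed for the effect therefore matters, and so would an estimate of how far workshops differ.

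Region is a separate and smaller matter. Blocks that serve only to equalise total numbers do not guarantee balance within a region. If workshops are regional, an uneven split would also leave one session thinly attended.

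**Working it through.** **Inputs from the article:** standardised effect 0.70; 32 per group; alpha 0.05; power 0.80; three regions. Sidedness is not stated; a two-sided test is used here because it reproduces the stated figure.

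**Inputs assumed, because the article gives none:** one workshop per region, so three workshops of 32/3 = 10.7 people; ICC of 0.01, 0.05 or 0.10. The ICC meant is that of the quantity compared between arms, in effect the change from baseline.

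**Step 1: reproduce the stated size.** For independent observations, n per group = 2 × ((1.960 + 0.842)/0.70)² = 2 × 16.02 = 32.04. Normal-approximation power at 32 per group is 0.800. The stated 32 is therefore the independent-observations figure and contains no allowance for shared sessions.

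**Step 2: allow for clustering in the intervention arm only.** With m people per workshop:
- design effect in that arm: DE = 1 + (m − 1) × ICC
- ratio of true to naive standard error: r = √((DE + 1)/2)
- type I error of the naive test: 2 × (1 − Φ(1.96/r))
- power with the correct standard error: Φ(0.70/(0.25 r) − 1.96), where 0.25 = √(2/32)

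For m = 10.7 and ICC 0.05: DE = 1 + 9.67 × 0.05 = 1.483; r = √(2.483/2) = 1.114; type I error = 2 × (1 − Φ(1.76)) = 7.9%; power = Φ(2.51 − 1.96) = 71%.

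| ICC (assumed) | DE | SE ratio | Type I error* | Power with correct SE |
|---|---|---|---|---|
| 0.01 | 1.097 | 1.02 | 5.6% | 78% |
| 0.05 | 1.483 | 1.11 | 7.9% | 71% |
| 0.10 | 1.967 | 1.22 | 10.8% | 63% |

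*Only if workshop effects vary around a mean of zero. Simulation of the naive t test (20,000 runs) gave 5.4%, 7.8% and 10.8%.

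**Step 3: vary the number of workshops.** With four workshops of 8, the ratios are 1.02, 1.08 and 1.16. With six of about 5.3, they are 1.01, 1.05 and 1.10. More and smaller sessions reduce the problem.

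**Step 4: read the result as interval coverage.** A nominal 95% interval for the average effect over workshops of this kind covers 100% minus the type I column: about 94.4%, 92.1% and 89.2%. This loss applies whatever the true mean effect. These are normal approximations; so few workshops would lower power further.

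**The case against.** **The article is condensed.** Strata, covariates and random effects are often left to the full protocol or analysis plan, and no two sections of the article conflict here. This stands as a limit. However, the article does commit to a sample size method, a purpose for the blocks and an analysis, and none of them shows an allowance for group delivery.

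**The size is unknown.** Much of the programme is individual or standardised: the online tutorial, the printed aid, the videos and a one-to-one telephone session. The article speaks of one workshop facilitator, and the outcome is a separate standardised call scored by blinded raters. A small ICC is plausible, and at 0.01 the effect is slight. This stands. Larger figures can be produced by assuming fewer, bigger sessions, but that sits badly with delivery in three home regions.

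**A reader might infer that the primary test is invalid.** The article does not support that. Randomisation is by individual, so if training affects nobody, sharing a room creates no correlation and the test keeps its level. Existing similarity within regions does not inflate the error either. Inflation needs workshops that truly differ, some helping and some harming, around a zero mean. Narrow coverage is the more general consequence.

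**A reader might infer that unstratified blocks bias the result or cause the narrow interval.** They do neither. Chance imbalance leaves a randomised comparison unbiased, and the repeated measures model removes stable baseline differences between regions. How uneven a region could become depends on entry order and block size, which are not given. If each region's staff are allocated consecutively, the blocks already hold them close to balance.

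**Conclusion.** The concern holds in a limited form. Group delivery in one arm is stated, 32 per group is the independent-observations figure, and the named ANOVA carries no workshop term. For any positive workshop ICC the reported interval is therefore too narrow. Under the three-workshop assumption, the shortfall in the standard error runs from negligible (about 2%) to appreciable (about 22%) over ICC 0.01 to 0.10. The direction follows from the design; the size rests wholly on an assumed ICC and workshop count.

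This is a worthwhile low-cost improvement, not a demonstration that the primary test fails. Regional stratification is secondary and is justified by precision alone.

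**What to change.** 1. Record which workshop session each intervention participant attends.
2. Prespecify a partially nested analysis as a sensitivity analysis of the primary result: a random workshop effect in the intervention arm only, with small-sample degrees of freedom. Report the ICC and say plainly that, from about three workshops, it will be very imprecise. If there is one workshop per region and region is in the model, the workshop term amounts to variation of the treatment effect between regions, and should be described so.
3. State the planned number and size of workshops.
4. For precision, have the external statistician prepare a separate permuted-block list for each of the three regions, and include region as a fixed factor in the primary model.

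**Cost:** three lists instead of one, two degrees of freedom for region, one extra field in the data, and a sensitivity interval that will be wider and itself imprecise. The sample size need not change for this, but the report should acknowledge that power may fall below 80% if workshops differ.
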